### Patient timeline and trial visits

Patients scheduled for elective abdominal surgery via a midline incision are screened preoperatively at day 0 (visit 1). Patients are enrolled given their ability to understand the extent and nature of the trial and their provision of written informed consent after detailed patient information. All inclusion criteria and no exclusion criteria must be fulfilled. Baseline data are collected during the screening/baseline visit. The duration of visit 1 will be approximately 25 min. Included patients are randomized during surgery (visit 2) after closure of the fascia in SST. Follow-up visits will be on postoperative days 5 to 7, 10 to 14 and 30 to 35 (visits 3–5) for evaluation of secondary endpoints (time expenditure approximately 15 min). In addition, 6, 12 and 24 months (visits 6–8) after surgery, patients are planned for follow-up to evaluate primary and secondary outcome parameters. The expenditure of time for each visit will be approximately 30 min per patient. An overview of trial visits and items captured during the trial visits is presented in Table 2 according to the guidelines of the Standard Protocol Items: Recommendations for Interventional Trials (SPIRIT) [29].

### Data management

All protocol-required information collected during the trial must be entered by the investigator, or designated representative, in an electronic case report form (eCRF) implemented in the Research Electronic Data Capture (REDCap™) system [31] (www.project-redcap.org). An explanation should be given for all missing data. The completed eCRF must be reviewed and signed by the investigator named in the trial protocol or by a designated sub-investigator. The Institute of Medical Biometry and Informatics of the University of Heidelberg (IMBI) is responsible for data management within the trial. To assure a safe and secure environment for any data acquired, data transmission is encrypted with Secure Sockets Layer (SSL) technology. Only authorized users are able to enter or edit data, and access is restricted to patients’ data in the respective centre. All changes to data are logged with a computerized timestamp in an audit trail. All data will be pseudonymized. Completeness, validity and plausibility of data will be checked in time of data entry (edit checks) and with the use of validating programs, which will generate queries. If no further corrections are to be made in the database, eCRF data will be locked. All data management procedures will be conducted according to written defined standard operating procedures (SOPs) of the IMBI that guarantee an efficient conduct complying with good clinical practice (GCP).

### Sample size calculation

The sample size calculation is based on the primary efficacy endpoint (IH risk) within 24 months after surgery. Based on the assumption that the percentage of patients developing an IH after midline laparotomy in a general surgical population closed with the SST is approximately 15% for the control group, we hypothesize a reduction of 7% in the intervention arm based on previous RCTs [13, 20]. Consequently, a sample size per group of 325 patients is needed for the between-group comparison by the chi-squared test to achieve 80% power in detecting this difference in IH risk at a two-sided level of significance of 5%. It is assumed that using a two-level logistic regression model adjusting for the random factor centre and the fixed factor IH risk (low-risk vs. high-risk patients: BMI ≥ 27 and/or surgery for abdominal aortic aneurysm) [20] in the primary analysis will lead to less unexplained variance and thus to an increased power. Assuming a drop-out rate of up to 20% based on previous trials [1, 3, 10, 18], a total of 812 patients (406 per group) will be randomized in the study (Fig. 1). The potential occurrence of missing values for the primary outcome is partially addressed by the predefined multiple imputation strategy. Sample size calculation was performed using ADDPLAN v6.1.

**Fig. 1 Fig1:**
[figure not shown]
Trial flow chart

### Analysis variables and statistical methods

The primary efficacy analysis will be based on the full analysis set (FAS) built according to the intention-to-treat (ITT) principle, thus reflecting the recommendations given in guidelines [32]. As a sensitivity analysis, an evaluation based on the per-protocol (PP) population (based on those patients without major protocol violation and excluding patients who receive a fascial closure not predefined in the randomization scheme) will be performed. The risk of IH will be analysed via a two-level binary logistic regression model including the fixed factors treatment group and IH risk (high vs. low), the latter being deemed as the most important confounder by far and being also used for stratification in the randomization procedure, and the random factor centre. Confounding by other less important prognostic and predictive factors can assumed to be controlled by the randomized study design. The model will be fitted using a variance-components covariance matrix. The level of significance is set to 5% (two-sided). All secondary outcomes will be evaluated descriptively, and descriptive *p* values will be reported together with 95% CIs for the corresponding effects.

### Further analyses

Interim analyses during the trial are not predefined or planned, but depending on the frequency of SAEs in both groups, safety analyses can be performed as recommended by the independent Data Safety Monitoring Board (DSMB). Further sensitivity analyses will be performed with the PP set, and the results will be compared with those of the ITT analysis. Moreover, for missing data in the ITT population set, further sensitivity analyses will be conducted by a worst-case scenario for the intervention, a minimal and a maximal IH risk imputation and by another alternative method of dealing with missing data as described by Higgins et al. [33]. Furthermore, a time-to-event analysis for the outcome “time from randomization to occurrence of IH” will be performed in the ITT population according to Kaplan-Meier. Additionally, prespecified subgroup analyses will be performed in the ITT population for the risk of incisional hernias in the subgroups of different types of surgery (colorectal, small bowel, hepatobiliary-pancreatic, upper GI (oesophageal and gastric), vascular, others), patients who are adipose vs. non-adipose and the presence or absence of neoadjuvant therapy, previous laparotomy or chronic obstructive pulmonary disease. All secondary outcomes will be evaluated descriptively, and descriptive *p* values will be reported together with 95% CIs for the corresponding effects.

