### Patient inclusion criteria

All patients scheduled for elective clean or clean-contaminated [25] abdominal surgery as defined by the Centers for Disease Control and Prevention (CDC) via a midline laparotomy for any indication will be screened consecutively for eligibility and will be informed about the HULC trial. All subjects must be able to understand the nature and extent of the trial, and only adult patients (> 18 years of age) with a life expectancy of at least 2 years who provide written informed consent will be included in the trial. The participant informed consent form includes general information about the trial (indication, clinical data about incisional hernias) as well as details about the experimental and control intervention, randomization, benefits and risks of participation in the trial and trial visits. Furthermore, it includes general study information like the voluntariness of participation, possibility of termination of the trial, organization and financing of the trial, data protection and important contact details for further questions. As the intervention of the trial includes two well-established surgical standard therapies for abdominal wall closure, there is no increased risk of any harm to be expected through participation in the trial. Thus, no additional compensation for any postoperative complications or harm is planned. Patients will be insured against travel accidents for their follow-up visits.

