### Primary endpoint

The primary outcome measure of the trial will be the occurrence of IHs within 24 months after surgery as defined by the European Hernia Society (EHS) [26]. Consequently, “any abdominal wall gap with or without a bulge in the area of a postoperative scar perceptible or palpable by clinical examination or imaging” is regarded as an IH. Occurrence of a burst abdomen will not be counted as a primary endpoint, but as a secondary endpoint by consensus [1, 3]. Follow-up time will be 24 months, as has been recommended by the EHS [26] since IH incidence increases over time [15]. Patients will be assessed for the primary endpoint at 6, 12 and 24 months after trial intervention. At these time points, patients will be examined by a clinician blinded for the trial intervention and by a radiologic examination performed by a blinded assessor. Radiologic exams allowed in the trial are sonography, computed tomography (CT) or magnetic resonance imaging (MRI) scans. In case of conflicting results between clinical and radiologic exams, the radiologic imaging is decisive to increase sensitivity [26]. If only one of the two examinations is performed (i.e. either clinical or imaging), the result of this assessment will be used for analysis. Possible results are listed in Table 1. As many patients included in this trial are expected to have an oncological indication for laparotomy and the included centres perform their oncological follow-up themselves, the loss to follow-up of patients is expected to be low. For patients who are unable or unwilling to attend the follow-up visits, a telephone follow-up is incorporated. The patient-reported outcome questionnaire developed by Jairam et al. [27] will be used, as it exhibits a high reliability. It will be used as a screening tool; i.e. patients who are suspected to have an IH based on the questionnaire might be convinced to attend an outpatient visit, even if they were reluctant to do so before.

**Table 1 Tab1:** Definition of the primary endpoint for the HULC trial

Clinical exam result	Imaging result	Primary endpoint for HULC
Hernia	Hernia	Hernia
No hernia	Hernia	Hernia
Hernia	No hernia	No hernia
No hernia	No hernia	No hernia
Hernia	Missing	Hernia
No hernia	Missing	No hernia
Missing	Hernia	Hernia
Missing	No hernia	No hernia

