### Primary estimand

In the recently released addendum to the ICH E9 guideline (draft version) [28], the estimands framework is recommended as a clear and transparent definition of “what needs to be estimated to address a specific scientific question of interest”. Such an estimand can be defined through the population of interest, variable of interest, specification of how intercurrent events are handled, and summary measure. The specification of how intercurrent events are handled is referred to here as intervention effect:
*Population*. The population is defined as all patients fulfilling all the inclusion and none of the exclusion criteria.*Variable*. The variable is the occurrence of IHs as defined by the EHS within 24 months after intervention.*Intervention effect*. Possible intercurrent events and the strategies to handle them are as follows: missing values due to death, drop-out, loss to follow-up and re-laparotomy will be replaced by using multiple imputation. Since re-laparotomy changes the probability of occurrence of an IH, information of occurrence or non-occurrence of IH after re-laparotomy will not be considered for primary analysis. This represents a hypothetical strategy for the post-randomization events re-laparotomy, drop-out, loss to follow-up and death. Except for these events, other post-randomization events will not be considered, thus reflecting a treatment policy approach, which means that the effect of randomized treatment is estimated irrespectively of other post-randomization events not captured in the primary endpoint definition.*Summary measure*. The summary measure is the odds ratio (OR). The OR will be calculated by a two-level binary logistic regression analysis including the fixed factors treatment group and IH risk (low vs. high), the latter being deemed as the most important confounder by far and being also used for stratification in the randomization procedure, and the random factor centre. Confounding by other less important prognostic and predictive factors can assumed to be controlled by the randomized study design. The model will be fitted using a variance-components covariance matrix. The level of significance is set to 5% (two-sided). The *p* value for judging the primary hypothesis will result from the two-level binary logistic regression model, where the coefficient of the factor treatment effect is tested against zero using the Wald test.

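### Kaplan-Meier is planned for time to hernia occurrence although hernia is assessed only at 6, 12 and 24 months; a visit-interval estimator would fit this supportive analysis

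*Protocol article*

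**What the plan says.** Under Further analyses, the protocol article plans one time-to-event analysis. Its outcome is the time from randomization to the occurrence of an incisional hernia, and it "will be performed in the ITT population according to Kaplan-Meier". The article does not say whether events are dated at nominal or actual visit times, or how death is treated in this analysis.

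Under Primary endpoint: "Patients will be assessed for the primary endpoint at 6, 12 and 24 months after trial intervention". Each of these visits comprises a blinded clinical examination and blinded imaging, and Table 2 schedules hernia assessment at no other visit. There is one route outside the schedule: "For patients who are unable or unwilling to attend the follow-up visits, a telephone follow-up is incorporated". It serves as a screen that may lead to an outpatient visit.

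The primary variable is binary: "The variable is the occurrence of IHs as defined by the EHS within 24 months after intervention". It is analysed by two-level logistic regression. On death and the other intercurrent events, Primary estimand states: "This represents a hypothetical strategy for the post-randomization events re-laparotomy, drop-out, loss to follow-up and death".

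**The concern.** The named outcome and the named estimator do not match. A hernia first seen at the 24-month visit arose at some point after the 12-month visit. Kaplan-Meier needs a date, and the only one available is the date of detection.

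The last visit adds a second difficulty. A patient found hernia-free there is censored on the very date on which a hernia would have been recorded. If actual dates are used, patients seen early in the final window leave the risk set while the others have not yet been examined. Late events are then divided by a shrinking number at risk. The level of the curve near month 24 then depends on how visit dates scatter, and its last steps rest on very few patients.

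The stake is a supportive curve. A cumulative hernia curve can still be read for absolute risk, and one that ends far above the true value would mislead.

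**Working it through.** **Inputs.** The article gives no figure for this analysis, so there is none to reproduce. Sample size calculation supplies the risks: 15% in control and 15 − 7 = 8% with mesh, with 325 per group. The two-proportion formula with pooled variance (two-sided 5%, 80% power) returns 325, so the inputs are read as the plan reads them.

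The following are assumed, because the article does not give them:
- The 15% splits into 5% by month 6, 4% in months 6-12 and 6% in months 12-24. The mesh arm has the same pattern scaled by 8/15.
- Final visits are spread evenly over months 23-25 or over months 24-25.
- There is no death or drop-out in steps 1 and 2.

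**Step 1: nominal visit times.** The survival factors are 0.95 at month 6, 0.91/0.95 at month 12 and 0.85/0.91 at month 24. Their product is 0.85, so 1 − KM at month 24 is 15%, which is correct. Between visits the curve is flat and lags. If onset has a constant hazard, the true control risk at month 18 is 1 − 0.85^0.75 = 11.5%, while the curve still shows its month-12 value, 1 − 0.85^0.5 = 7.8%. With mesh the values are 6.1% and 4.1%.

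**Step 2: actual visit dates.** Among patients hernia-free at month 12 (0.91), the chance of detection at the final visit is h = 0.06/0.91 = 0.0659. Let F(t) be the share of them whose final visit has taken place by time t. Every patient leaves the risk set at that visit, with or without a hernia, so KM survival is approximately 0.91 × (1 − F(t))^h.
- Final visits in months 23-25: F(24) = 0.5, and 1 − 0.91 × 0.5^0.0659 = 1 − 0.91 × 0.955 = 13.1%. Simulation with 325 per arm gives 13.0-13.1%. Any symmetric window has F(24) = 0.5, so ±0.5 month gives the same.
- Final visits in months 24-25: F(24) = 0, so 1 − 0.91 = 9.0%. Simulation gives 9.0-9.1%.
- End of the curve: expected survival is 0.91 × ∏(1 − h/k), with k from 1 to m = 0.91 × 325 ≈ 296. The product is 0.659, so 1 − 0.91 × 0.659 = 40.0%. Simulation gives a mean of about 40% and a median of 34%. With probability h, about 6.6%, the last patient examined has a hernia and the curve jumps to 100%.

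For mesh, h = 0.032/0.952 = 0.0336. The same formulas give 7.0% and 4.8% at month 24. At the end of the curve they give 1 − 0.952 × 0.808 = 23.1%.

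A separate simulation with constant-hazard onset, 406 per arm and windows of ±0.5 or ±1 month gives about 12-13% at month 24 and 43-48% at the end in control. With mesh it gives about 6.6% and 26-28%. The result does not hinge on the assumed split.

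**Step 3: death.** Assume constant independent hazards, with λh = −ln 0.85 = 0.1625 and λd = −ln(1 − q) for mortality q by month 24. Then cumulative incidence = λh/(λh + λd) × [1 − 0.85(1 − q)].

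| Assumed q | Calculation | Cumulative incidence | Below 15% by |
|---|---|---|---|
| 5% | 0.1625/0.2138 × 0.1925 | 14.6% | 0.4 points |
| 10% | 0.1625/0.2679 × 0.2350 | 14.3% | 0.7 points |
| 20% | 0.1625/0.3857 × 0.3200 | 13.5% | 1.5 points |

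If a hernia counts only when it is detected at a visit while the patient is alive, the incidences are 14.5%, 14.0% and 12.9%.

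**The case against.** A reader might infer that the curve cannot estimate the 24-month risk at all. The article does not support that. It does not prescribe actual dates, and with nominal times and independent censoring the month-24 value is right. The 13%, 9% and 40% figures belong to one implementation with assumed windows, and the dating convention may be set in an analysis plan that is not shown. This objection stands and limits the point. It does not remove it: nominal dating still leaves an estimator of detection for an outcome defined as occurrence.

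A reader might also infer that censoring deaths is an error, or that no planned analysis gives the risk patients actually experience. Neither follows. Censoring deaths targets the same no-death risk as the hypothetical strategy under Primary estimand. That section adds that supplementary estimands exist but are not detailed, and Further analyses plans a minimal-risk imputation that may count deaths as hernia-free. Mortality of 20% would also use up the whole drop-out allowance, and eligibility requires patients "with a life expectancy of at least 2 years who provide written informed consent". On the other side, "As many patients included in this trial are expected to have an oncological indication for laparotomy", so death is not negligible.

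It would also go too far to say that hernias can be found only at the three visits, since the telephone screen may prompt another visit.

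The relative contrast at month 24 is nearly preserved: 15/8 = 1.88 in truth, against 13.1/7.0 = 1.87 and 9.0/4.8 = 1.88. The absolute difference is not. It falls from 7.0 points to 13.1 − 7.0 = 6.1 or 9.0 − 4.8 = 4.2, and absolute risk is what such a curve displays.

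Finally, the analysis is supportive. The 24-month risk is tested by the logistic model, and nothing here touches that test.

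**Conclusion.** The point holds as a mismatch between outcome and estimator in a supportive analysis. Onset is interval-censored by the visit schedule, so Kaplan-Meier gives time to detection. With nominal visit times, only the shape between visits is wrong, for example 7.8% against 11.5% at month 18 in control under constant-hazard onset. With actual dates, a true 15% reads about 13% or 9% at month 24 under the two assumed windows, and about 40% on average at the end of the curve, which is then unusable.

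The treatment of death is a choice of estimand and not a fault. Its size is about 0.4 to 1.5 points in the control arm for an assumed mortality of 5-20%. The visit windows, the onset pattern and the mortality are assumptions. The primary analysis and the sample size are unaffected.

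**What to change.** Replace Kaplan-Meier in this supportive analysis by one of two methods:
- a Turnbull estimate by arm, with each hernia placed between the last hernia-free examination and the examination that found it; or
- a discrete-time complementary log-log model on the intervals 0-6, 6-12 and 12-24 months, with treatment, hernia-risk stratum and centre (random, as in the primary model).

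Report the estimated risk by arm at 6, 12 and 24 months. A hernia found between scheduled visits fits either method through the interval in which it was found.

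State that deaths are censored, in line with the hypothetical strategy of the primary estimand. If the risk that patients actually experience is also of interest, add a cumulative incidence with death as a competing event alongside this analysis, not in its place.

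The cost is a sentence or two of wording and modest programming. No new data or visits are needed, and the primary test and sample size stay as they are.

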### Safety analysis

The assessment of safety will be based on the frequency of SAEs in both groups, which will be analysed via descriptive statistical methods in the study population. For comparisons of frequencies between groups, the chi-squared test will be used. All analyses will be done using SAS version 9.4 or higher.

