### Patients and trial centres

To enrol the required number of patients in the planned recruitment period, 12 trial sites of the Clinical Trials Network of the German Surgical Society (CHIR-*Net*) will participate in this trial (www.chir-net.de). These 12 centres will be high-volume centres committing to include at least 50 patients each. To improve recruitment at all centres, brochures and flyers for patients including information about the trial will be available.

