### Assignment of intervention and randomization

In order to ensure equal distribution of patient characteristics, randomization will be used. Allocation of treatments will be performed using a web-based randomization tool (www.randomizer.at) by means of block-wise randomization. Randomization will be performed intraoperatively at the end of surgery, after closure of the fascia. This prevents potential bias by different intraoperative techniques. Before randomization, the surgeon needs to confirm a clean or clean-contaminated operation according to CDC definition [25]. Randomization will be stratified by centre and by IH risk (low-risk vs. high-risk patients, defined as patients with body mass index (BMI) ≥ 27 and/or those having surgery for abdominal aortic aneurysm). The surgeon who will perform the closing technique must be chosen before abdominal wall closure. As randomization is performed after closure of the facia in SST, surgeons call their respective clinical trial centre to have the online randomization performed and to receive the results by phone. Alternatively, the online randomization can be performed in the operating room by a third person, if the necessary equipment and internet access is available.

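### SAE frequencies are compared by an unstratified chi-squared test although randomisation is stratified by centre and IH risk: a valid test, but mildly conservative if those factors predict SAEs

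*Protocol article*

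**What the plan says.** All references are to the protocol article.

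- **Safety analysis.** Safety rests on SAE frequencies in the two groups, "which will be analysed via descriptive statistical methods in the study population". The next sentence names the test: "For comparisons of frequencies between groups, the chi-squared test will be used". It mentions no stratification or adjustment, and no significance level, hypothesis or decision threshold is attached to it.
- **Assignment of intervention and randomization.** Allocation is made "by means of block-wise randomization", and "Randomization will be stratified by centre and by IH risk". High risk means a BMI of 27 or more and/or surgery for abdominal aortic aneurysm.
- **Patients and trial centres.** There are "12 trial sites of the Clinical Trials Network of the German Surgical Society", which with two risk levels gives 12 × 2 = 24 strata.
- **Primary estimand** and **Analysis variables and statistical methods.** The IH endpoint is analysed by a two-level logistic model with treatment and IH risk as fixed factors and centre as a random factor. IH risk is included for a stated reason: "the latter being deemed as the most important confounder by far and being also used for stratification in the randomization procedure".

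**The concern.** Block randomisation within strata keeps the two arms close to balanced in every combination of centre and risk level. Differences in SAE risk between strata then largely cancel from the comparison of arms. The plain chi-squared test takes its variance from the pooled event rate and still counts those differences. If they exist, the standard error is somewhat too large, the true error rate falls below the nominal one, and power is lost. For a comparison of harms, that means slightly less chance of seeing a true excess in the mesh arm.

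The comparison has uses. Under Further analyses, safety analyses recommended by the DSMB depend on how often SAEs occur in each group, and the Discussion promises that the trial will allow benefit to be weighed against risk. As written, benefit is analysed with the design factors and SAEs without them.

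Some link between strata and SAEs is plausible. The trial admits any indication, the planned subgroups run from small bowel to oesophageal and vascular surgery, and Key secondary endpoints says that organ-space infections depend on the underlying operation and may count as SAEs. How much SAE risk differs between centres or risk levels is nowhere stated.

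**Working it through.** **1. The plan's own figure.** The article gives no figure for the safety comparison. Its sample size for the primary endpoint (15% vs 8%, two-sided 5%, 80% power, chi-squared test) can be reproduced:

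n = [1.960 × √(2 × 0.115 × 0.885) + 0.842 × √(0.15 × 0.85 + 0.08 × 0.92)]² / 0.07² = (0.884 + 0.377)² / 0.0049 ≈ 325 per group, as stated.

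Allowing for 20% drop-out, 325 / 0.8 = 406.25, in line with the stated 406 per group and 812 in total. The safety question therefore concerns about 406 patients per arm.

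**2. Why the test is conservative, and when.** Let stratum s hold a share w_s of the patients and have event risk p_s. Let p̄ be the average risk, with n patients per arm, balance within strata and no treatment effect.

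- True variance of the difference in proportions: (2/n) Σ w_s p_s(1 − p_s).
- Variance used by the chi-squared test: (2/n) p̄(1 − p̄) = (2/n) [Σ w_s p_s(1 − p_s) + Σ w_s(p_s − p̄)²].
- Ratio of true to assumed variance: r = 1 − Σ w_s(p_s − p̄)² / [p̄(1 − p̄)], which is never above 1.
- Actual type I error: 2[1 − Φ(1.96/√r)].

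If all strata share the same risk, r = 1 and nothing is lost. Otherwise the error rate is below 5%, never above it.

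**3. Simulation.** From the article: 12 centres, 2 risk levels, equal arms. Assumed, because the article gives no values:

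- 24 equal strata with 17 patients per arm in each (408 per arm)
- exact balance within strata, which gives an upper bound on the effect
- average control SAE rate of 10%, 20% or 30%
- normal centre effects on the logit scale with the SD shown
- the odds ratio (OR) shown for high vs low IH risk

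The true treatment OR was 1.80, 1.59 or 1.51 for the three rates, set for about 80% power of the plain test without heterogeneity. There were 40,000 runs per scenario, each test at two-sided 5%.

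| SAE rate | Centre SD, risk OR | Type I error: chi-squared / CMH | Power: chi-squared / CMH | Loss (points) |
|---|---|---|---|---|
| 10% | 0, 1 | 0.050 / 0.050 | 80.6 / 80.7 | 0.0 |
| 10% | 0.3, 1.5 | 0.048 / 0.050 | 79.7 / 80.1 | 0.4 |
| 10% | 0.5, 2 | 0.048 / 0.051 | 76.8 / 77.9 | 1.1 |
| 10% | 0.8, 3 | 0.042 / 0.050 | 71.5 / 74.6 | 3.1 |
| 20% | 0, 1 | 0.049 / 0.049 | 80.2 / 80.2 | 0.0 |
| 20% | 0.3, 1.5 | 0.048 / 0.050 | 78.7 / 79.2 | 0.6 |
| 20% | 0.5, 2 | 0.043 / 0.049 | 75.5 / 77.3 | 1.8 |
| 20% | 0.8, 3 | 0.036 / 0.049 | 68.8 / 73.6 | 4.8 |
| 30% | 0, 1 | 0.051 / 0.051 | 80.3 / 80.3 | 0.0 |
| 30% | 0.3, 1.5 | 0.047 / 0.050 | 78.3 / 79.0 | 0.7 |
| 30% | 0.5, 2 | 0.042 / 0.050 | 75.0 / 77.2 | 2.2 |
| 30% | 0.8, 3 | 0.034 / 0.048 | 67.1 / 72.9 | 5.8 |

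Losses are taken from unrounded power.

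**4. A second simulation with actual blocks.** It assumed 12 centres of 68 patients, half of them high risk, blocks of 4, a 30% SAE risk, a risk OR of 1.5 to 2.0, a centre SD of 0.3 to 0.8 and a treatment OR of 1.5, with 6,000 trials per scenario. Chi-squared type I error ran from 4.9% down to 3.3%, against 4.6% to 5.3% for the stratified test. Power ran from 75.6% down to 67.6%, against 76.5% down to 72.2%. The losses are 76.5 − 75.6 = 0.9 and 72.2 − 67.6 = 4.6 points, of the same order as above.

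**5. How strong the last scenario is.** A centre SD of 0.8 around a 30% rate puts 95% of centres within −0.847 ± 1.96 × 0.8 on the logit scale, which is an SAE risk of roughly 8% to 67%.

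**The case against.** The strongest case against raising this is that nothing here is wrong. A plain chi-squared test is a usual choice for SAE tables, it does not inflate the type I error, and no other part of the article conflicts with it. The section calls the analysis descriptive. The two-sided 5% level is set for the IH endpoint, not for this test. Closing the trial early is decided by the Steering Committee with DSMB advice on safety reports, and no rule there uses this p value. IH risk was chosen because it predicts hernias, and the article does not say that it predicts SAEs. All of this stands, and it limits the point to an optional refinement.

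It does not remove the point altogether. The test is a stated choice, not a detail left open. Its direction under heterogeneity follows from the variance identity. In the simulations the stratified test lost nothing even when the strata were irrelevant.

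A reader might infer three stronger things, none of which the documents support:

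- **That the plan is set to overlook harm from the mesh.** This would need strata known to predict SAEs strongly and a decision tied to the test. The article shows neither.
- **That wound infection, seroma, haematoma and burst abdomen are affected too.** These are key secondary endpoints, for which the article promises descriptive p values and 95% CIs but names no test. They are outside this point.
- **That benefit and harm must be analysed identically.** A confirmatory primary endpoint and descriptive safety tables are normally handled differently.

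**Conclusion.** The point holds as a small, conditional loss of efficiency. The direction is certain: ignoring stratification factors that predict the outcome makes the plain test conservative. The size is not known from the documents. It is zero if centre and IH risk are unrelated to SAEs, about 0.4 to 2 points of power under mild to moderate heterogeneity, and 3 to 6 points only under strong heterogeneity. These figures rest on assumed SAE rates, centre SDs, risk ORs, stratum sizes and either exact balance or blocks of 4. The sample size, the primary analysis and the validity of the safety comparison are unaffected. Optional.

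**What to change.** In Safety analysis, replace the chi-squared sentence with one stating that the proportion of patients with at least one SAE will be compared by a Cochran-Mantel-Haenszel test stratified by centre and IH risk. Alternatively, name the two-level logistic model already specified under Analysis variables and statistical methods (treatment and IH risk fixed, centre random). In either case, report the effect estimate and its 95% CI from the same analysis, and keep the analysis labelled descriptive.

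The cost is one sentence. It needs no new data, since centre and IH risk are recorded for randomisation, and no change to the sample size. In the scenarios simulated, the Cochran-Mantel-Haenszel test kept its error rate close to 5% and lost no power when the strata did not matter.
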